**Methods and design:**

We plan to recruit 150 women with POI from four participating hospitals in China. Participants will be randomized in a 1:1 to receive oral BSHX or BSHX placebo. All participants will be treated for 3 months and will be followed up for another 3 month. The primary outcome is questionnaire scores based on the changes in the total symptoms, which is the Chinese version of the Menopause-Specific Quality of Life (CMS) (Nie G, Yang H, Liu J, Zhao C, Wang X, Menopause 24(5):546–554, 2017). CMS will be measured before the intervention, at 3 months and 6 months after randomization for all participants. The other measurements include serum sex hormone levels, anti-Müllerian hormone (AMH) levels, ovarian peak systolic velocity (PSV; cm/s), and antral follicle count (AFC). In this study, the regulatory effects of traditional Chinese medicine on hormones were evaluated by the changes of serum sex hormone levels, which include serum estradiol (E2), luteinizing hormone (LH), and follicle-stimulating hormone (FSH). These indicators will be measured before intervention and at 3 months after randomization.

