### Safety assessments

Studied medicine safety testing includes liver and renal function test, blood routine examination, urine routine examination, stool routine examination, and electrocardiogram. These parameters will be obtained both at screening and after treatment, and all samples were tested by the Jiangsu Province Hospital on Integration of Chinese and Western Medicine in China. Standardized protocols exist at the study center regarding the management of known of potential adverse effects. Adverse events related to the intervention will be monitored through review of the patient’s records, participant self-report, and by the clinicians. All adverse events during treatment and follow-up will be recorded and analyzed in detail. If a participant has a serious adverse event and was not safe to continue the trial, the participants were requested to withdraw from the trial. Immediate relevant treatments were provided to those participants, and following up continued until the response was terminated.

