#### Secondary outcomes

The secondary measurements included serum sex hormone levels, AMH, AFC, and PSV (cm/s). The regulatory effect of tested medicine on hormone balance was monitored by the level of serum sex hormones (FSH, LH, E2). The blood samples of all subjects were taken in the early antral follicular phase before treatment and after the withdrawal of the drug. As an ovario specific growth factor, AMH is an effective and reliable indicator to predict ovarian reserve function [26], and it has no cycle-dependent [27]. AFC is helpful to evaluate the relative accuracy of ovarian reserve function when used in combination with sex hormone detection and can also provide a reference for the formulation of the treatment plan [28]. Transvaginal ultrasound is the best way to observe AFC indicators, which can be accurately evaluated and calculated the number of follicles. Generally, the AFC is measured at the beginning with the early antral follicular stage. Transvaginal ultrasound is performed by an experienced ultrasound expert, and the follicle count of both ovaries with a diameter of 2–10 mm (measured by clinicians rather than automatically calculated) is used to calculate AFC. All subjects underwent vaginal ultrasound examination at the follicular stage before treatment and after drug withdrawal.

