### Statistical analysis

Data will be analyzed with SPSS V.21 (IBM) by statisticians independent from involved researchers in this study. Efficacy and safety will be evaluated by intention-to-treat (ITT) analysis within the full analysis set (FAS) according to the ITT principle. At the same time, per-protocol (PP) analysis will apply to evaluate data collected from subjects who have completed all steps of the trial protocol. Results of the full analysis set and the per-protocol set will be compared. All prespecified outcomes will analyze in the ITT population because ITT analysis often underestimates the efficacy and was usually conservative. On the contrary, PP analysis overestimates the efficacy and the differences between the two groups. Therefore, this study mainly uses ITT analysis, and PP analysis will be applied if there was a statistical significance. Various assignment methods were used to detect whether the results of different assumptions of missing data are robust. The safety evaluation will be conducted by ITT analysis.

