Descriptive analysis will be used for baseline variables including demographic characteristics, medical history, course of disease, treatment history, combined diseases, concomitant medications, vital signs, laboratory tests for safety assessment, and adverse events. Continuous variables will be expressed by mean ± SD; categorical variables will be shown as counts and percentages. Estimates of the adjusted differences in risks are presented with 95% confidence intervals (CIs) of the difference. The comparability of the characteristics between the BSHX and placebo groups will be assessed by using *t*-test for continuous variables with normal distribution, while the non-parametric Mann-Whitney-Wilcoxon test will be used for the comparison of data with non-normal distribution. Specifically, the paired *t*-test will be used to compare the difference of the outcome between preintervention and postintervention in each group and independent t-test will be used to compare the difference between the two groups. Categorical variables will be compared using *Χ*^2^ statistics, while the Fisher exact test will be used when the theoretical frequency is less than 5 in more than 25% of the cells. In order to control the center and baseline effects, covariance analysis will be applied for the intergroup comparison with continuous variables and Cochran-Man-tel-Haenszel test for categorical variables. The differences of CMS scores, levels of FSH, LH, E2, AMH, the AFC, and ovarian PSV (cm/s) at month 0 and month 3 between the BSHX and placebo groups will be compared using an independent *t*-test. A repeated-measures analysis of variance (ANOVA) test with Bonferroni post hoc test will be used to evaluate the changes in CMS scores, levels of FSH, LH, E2, AMH, the AFC, and ovarian PSV (cm/s) and safety assessment measurements throughout the experiment. In all tests, a value of *p* < 0.05 will be considered statistically significant. All statistical analyses will be performed using SPSS V.20.0.

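### Repeated-measures ANOVA with Bonferroni is a weak method for the three-visit CMS course and a redundant one for outcomes measured only twice

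*Protocol article*

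**What the plan says.** All references are to the protocol article.

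- **Method and scope (Statistical analysis).** "A repeated-measures analysis of variance (ANOVA) test with Bonferroni post hoc test will be used to evaluate the changes in CMS scores". The same sentence goes on to FSH, LH, E2, AMH, AFC, PSV "and safety assessment measurements throughout the experiment".
- **CMS schedule (Abstract, Methods and design).** "CMS will be measured before the intervention, at 3 months and 6 months after randomization for all participants": three assessments.
- **Other efficacy outcomes.** The abstract says "These indicators will be measured before intervention and at 3 months after randomization". Secondary outcomes agrees: blood is taken "in the early antral follicular phase before treatment and after the withdrawal of the drug", and for ultrasound, "All subjects underwent vaginal ultrasound examination at the follicular stage before treatment and after drug withdrawal". That is two assessments.
- **Safety tests (Safety assessments).** "These parameters will be obtained both at screening and after treatment": two assessments.
- **Other planned comparisons (Statistical analysis).** Independent t-tests compare the groups at months 0 and 3. Covariance analysis is planned to control for centre and baseline, with no visit named.
- **Population and missing data.** "All prespecified outcomes will analyze in the ITT population". The section on removal and dropout has a dropout's last recorded data analysed, and Statistical analysis mentions several imputation methods as robustness checks.

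**The concern.** The t-tests stop at month 3 and the covariance analysis names no visit, so the repeated-measures ANOVA carries the CMS course including month 6. It does that poorly, for three reasons.

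1. The month-0 score is measured before randomisation and cannot reflect treatment. Making it one of the repeated outcomes uses it less efficiently than adjusting for it.
2. With three visits the group-by-time test has 2 degrees of freedom. It asks whether the two mean profiles differ in any way. It gives no treatment difference at month 3 or at month 6, and these are different questions: end of treatment, and three months off drug.
3. The classical method needs a complete record from each woman. Either women without a month-3 or month-6 CMS are lost, or their values are filled in. The article does not say which data the ANOVA uses.

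For outcomes measured twice, the method does not fit the plan's own schedule. At stake are power and the clarity of the answer on the primary outcome, plus a superfluous test on each of the others.

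**Working it through.** **Plan's own figure.** The article gives no power for the ANOVA. Its sample size rests on a two-group difference in means, so there is no ANOVA figure to reproduce. (The printed formula with the printed quantiles gives 2 × [(1.64 + 1.28) × 7.42 / 2.9]² = 111.6 per group, not 70. That is a separate matter, but it explains why even the better analysis falls short of 90% here.)

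**Inputs from Sample size calculation.** Month-3 effect 2.9; SD 7.42, so σ² = 55.06; 150 women; up to 15% dropout.

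**Assumptions not in the article.** A further 8% missing at month 6; correlation r between any two visits of 0.5 or 0.7; month-6 effect of 0, 1.45 or 2.9; missingness unrelated to outcome; two-sided 5% tests; 7.42 read as the SD of a single score. At r = 0.5 the SD of a change equals that of a score, since 2(1 − r) = 1, so that row also holds if 7.42 is the SD of change.

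**Women available.** Month 3: 150 × 0.85 = 127.5. All three visits: 127.5 × 0.92 = 117.3, or 58.65 per group.

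**CMS, group-by-time test on complete cases.** With n per group and group differences d at the three visits, the noncentrality is λ = (n/2) × Σ(d − mean d)² / [σ²(1 − r)], on 2 and 2(N − 2) degrees of freedom.

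- Differences (0, 2.9, 0): 8.41 − 2.9²/3 = 5.607. Differences (0, 2.9, 2.9): 16.82 − 5.8²/3 = 5.607.
- Differences (0, 2.9, 1.45): 10.5125 − 4.35²/3 = 4.205.
- r = 0.5: λ = 29.325 × 5.607 / 27.53 = 5.97, or 29.325 × 4.205 / 27.53 = 4.48.
- r = 0.7: dividing by 16.52 instead gives λ = 9.95 or 7.47.

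**CMS, month-3 ANCOVA.** λ = n × 2.9² / [2σ²(1 − r²)] with n = 63.75 and 1 degree of freedom.

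- r = 0.5: 536.1 / 82.58 = 6.49.
- r = 0.7: 536.1 / 56.16 = 9.55.

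| Power from these λ | r = 0.5 | r = 0.7 |
|---|---|---|
| ANOVA, N = 117.3, month-6 effect 0 or 2.9 | 57.6% | 80.8% |
| ANOVA, N = 117.3, month-6 effect 1.45 | 45.3% | 67.9% |
| ANOVA, N = 127.5, month-6 effect 0 or 2.9 | 61.5% | 84.2% |
| ANOVA, N = 127.5, month-6 effect 1.45 | 48.8% | 71.9% |
| ANCOVA at month 3, N = 127.5 | 71.5% | 86.6% |

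Simulations agree: ANOVA 44–59% and 66–82%; ANCOVA 70–72% and 86–87%.

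**Where the gap comes from.** Restoring the deleted women (117.3 to 127.5) gains only 3 to 4 points in every scenario. At r = 0.5 the total gap is 13.9 or 26.2 points, so most of it is due to the 2-degree-of-freedom test and the handling of baseline. At r = 0.7 the same holds for a month-6 effect of 1.45 (gap 18.7). For an effect of 0 or 2.9 the gap is only 5.8 points, of which deletion explains 3.4.

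**Carrying the last value forward.** All 150 women stay in. The 15% lost by month 3 then contribute their baseline score, that is, no change, so the expected month-3 effect is 0.85 × 2.9 = 2.465, about 2.5. Simulated ANOVA power is about 48–63% (r = 0.5) and 73–85% (r = 0.7), still below ANCOVA.

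**Outcomes measured twice.** With differences (0, d), Σ(d − mean d)² = d²/2, so λ = n d² / [4σ²(1 − r)]. This is exactly the noncentrality of the t-test on change, whose variance is 2σ²(1 − r). In one simulated data set, F and t² were both 13.972. Two visits give one pairwise comparison, so Bonferroni divides 0.05 by 1. With three CMS visits there are three comparisons, at 0.05/3 = 0.0167 each.

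**The case against.** A reader might infer that the ANOVA drops every woman with a missed visit and so contradicts the ITT commitment. The article does not say that. It provides for last recorded data and for imputation, and on filled-in data all 150 women remain. Nor would most missed visits matter: of the nine follow-ups listed, only a missing CMS at month 3 or month 6 has any effect. Which data set the ANOVA uses may properly be settled in the full protocol or SAP.

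A second tempting reading is that the primary comparison has only 44–59% power. That does not follow either. The ANOVA is nowhere named as the primary test, covariance analysis adjusting for baseline and centre is already planned, and the month-3 difference is also tested by t-test.

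A third is that the ANOVA is invalid for the twice-measured outcomes. It is not: it returns the same p-value as the t-test on change.

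It is also fair to say that the 8% loss and both correlations are assumed, that at r = 0.7 the ANOVA comes close to ANCOVA in some scenarios, and that the proposed mixed model was not itself simulated.

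What stands after all this is that the article fixes a method for the whole CMS course. That method is weaker than the adjusted analysis on complete or carried-forward data in every scenario examined, and it does not give the treatment difference at each visit.

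**Conclusion.** The point holds as a worthwhile improvement, not as a fatal flaw.

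For CMS, the named method has about 44–59% power at r = 0.5 and 66–82% at r = 0.7 on complete cases, against about 71% and 87% for month-3 ANCOVA. The comparison rests on the plan's 2.9 and 7.42 and on the assumed missingness and correlations. Deletion is generally the smaller part of the deficit, so imputing values would not cure it, and carrying the last value forward would also shrink the month-3 effect to about 2.5.

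For hormones, AMH, AFC, PSV and safety tests, the ANOVA and its Bonferroni step are redundant. They alter no estimate or error rate, and removing them only tidies the plan.

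**What to change.** **CMS.** Replace the repeated-measures ANOVA with a linear mixed model on the month-3 and month-6 scores. Include treatment, visit, treatment-by-visit, baseline CMS and centre, with an unstructured covariance, and use all observed data. Report the treatment difference with its confidence interval at each visit. The model assumes that missingness depends only on observed data; the imputation analyses already foreseen can serve as sensitivity checks. If women lost by month 3 also have no month-6 score, the month-3 contrast rests on the same women as the month-3 ANCOVA, so similar power is expected there.

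**Outcomes measured twice.** Use the covariance analysis already planned, stated as the month-3 (post-treatment) value adjusted for baseline and centre, and delete the repeated-measures ANOVA and Bonferroni step.

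**Cost.** Analysis wording only. No additional data or visits are needed, and the named software can fit the model. The change should be made and dated before unblinding.

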## Ethics and dissemination

The protocol has been approved by the Ethics Committee of Jiangsu Province Hospital on Integration of Chinese and Western Medicine. (No. 2019LWKY014). It has been registered in the Chinese Clinical Trial Registry (ChiCTR1900028451). The data of this trial will be managed by ResMan at http://www. medresman. org/ and posted on Chinese Clinical Trial Registry. Results from this study will be published to the public through social media, academic conferences, and peer-reviewed journals.

## Discussion

To our knowledge, this is the first study protocol of a randomized, double-blinded, placebo-controlled, multicenter clinical trial for POI treatment. The results from this trial will provide reliable evidence for the application of Chinese medicine BSHX in the treatment of POI. Report of this randomized controlled trial has been complied according to the Consolidated Standards of Reporting Trials for TCM statement [29]. This clinical trial protocol followed quality methodology and strictly enforced quality control. A standardized preparation of traditional Chinese medicine particles, record screening, randomization process, verification of biomarkers, and objective measurement were formulated by this study. Detailed methods of distribution hiding, recruitment, randomization, and data collection were also obtained. Based on previous studies, we have concluded that the most important clinical efficacy evaluation method of Chinese herbal medicine is the effect of Chinese herbal medicine on specific symptoms of diseases. Symptoms last for several years in many POI cases, and this seriously affects the quality of life of patients. Therefore, it is imperative and necessary to search for medicines that can significantly alleviate symptoms with no adverse reactions in the long term. Results from previous clinical trials have shown that BSHX can effectively relieve clinical symptoms, regulate hormone levels, and restore menstrual cycle and menstrual flow [30]. Other studies also demonstrated BSHX has the effect of improving the luteal function, improving the pregnancy rate, and enhancing the body’s immunity [31]. It has good clinical effect and is an effective prescription. Modern pharmacological studies suggest that Chinese herb medicines in BSHX can effectively regulate female hypothalamus-pituitary-ovarian reproductive axis and promote follicle growth and maturity, with strong estrogen-like action. For example, Cuscuta, one of the Chinese herb medicines in BSHX, enhances the function of human chorionic gonadotropin (HCG) and LH receptors of ovary and pituitary to release gonadotropin release hormone (LRH) reactivity [32]. Epimedium can directly act on the hypothalamus and promote the pituitary releasing hormone and has a gonadal-like effect with direct adjustment function [33]. Previous papers indicated that blood activating drugs can improve ovarian reactivity, inhibit the activity of anti-ovarian antibodies, and reduce the ovarian autoimmune damage by improving ovarian blood supply [34]. Results from the abovementioned studies are obvious evidences that BSHX is effective and safe for POI treatment. The main purpose of this study is to explore the factors of diagnosis or treatment rather than pathogenesis. It is, therefore, important to further investigate the underlying mechanism of BSHX in POI treatment in humans, such as exploration of POI-related signal pathway regulation, the requirements of POI disease itself. These studies in the future are expected to open up new ideas for the treatment of POI.

## Trial status

The protocol version number is 1.3, dated January 10, 2020. After getting the ethical approval, there have been minor protocol modifications because of the COVID-19 pandemic as described above, which was communicated at the time with involved wards. And re-report to the ethics committee in a timely manner. These changes have no impact on the study conduct. Recruitment began in February 2020 and is expected to complete patient follow-up by the end of November 2021.

## Protocol amendments

Any protocol amendments will be communicated to the sponsor (Jiangsu Province Hospital on Integration of Chinese and Western Medicine), the relevant research ethics committee, and the study participants.

## Data Availability

We declared that materials described in the manuscript, including all relevant raw data, will be freely available to any scientist wishing to use them for noncommercial purposes without breaching participant confidentiality. Access to the protocol and the dataset may be provided upon request to the authors.
